## Abstract

**Background:**

Preserved residual kidney function (RKF) and normal fluid status are associated with better patient outcomes in incident haemodialysis patients. The objective of this trial is to determine whether using bioimpedance technology in prescribing the optimal post-dialysis weight can reduce the rate of decline of RKF and potentially improve patient outcomes.

**Methods/Design:**

516 pateints commencing haemodialysis, aged >18 with RKF of > 3 ml/min/1.73 m^2^ or a urine volume >500 ml per day or per the shorter inter-dialytic period will be consented and enrolled into a pragmatic, open-label, randomized controlled trial. The intervention is incorporation of bioimpedance spectroscopy (BI) determination of normally hydrated weight to set a post-dialysis target weight that limits volume depletion, compared to current standard practice. Clinicians and participants will be blinded to BI measures in the control group and a standardized record capturing management of fluid status will be used in all participants. Primary outcome is preservation of residual kidney function assessed as time to anuria (≤100 ml/day or ≤200 ml urine volume in the short inter-dialytic period). A sample size of 516 was based upon a cumulative incidence of 30% anuria in the control group and 20% in the treatment group and 11% competing risks (death, transplantation) over 10 months, with up to 2 years follow-up.

Secondary outcomes include rate of decline in small solute clearance, significant adverse events, hospitalization, loss of vascular access, cardiovascular events and interventions, dialysis efficacy and safety, dialysis-related symptoms and quality of life. Economic evaluation will be carried out to determine the cost-effectiveness of the intervention. Analyses will be adjusted for patient characteristics and dialysis unit practice patterns relevant to fluid management.

**Discussion:**

This trial will establish the added value of undertaking BI measures to support clinical management of fluid status and establish the relationship between fluid status and preservation of residual kidney function in incident haemodialysis patients.

**Trial registration:**

ISCCTN Number: 11342007, completed 26/04/2016; *NIHR Portfolio number:* CPMS31766; *Sponsor*: Keele University

## Background

Preservation of residual kidney function (RKF) and achieving normal volume status are recognized as two linked and critically important predictors of survival in haemodialysis patients. The CANUSA study found that each 250 ml of urine per day increased 2-year survival by 36% in peritoneal dialysis patients [1] and in the NECOSAD study complete anuria in haemodialysis (HD) patients increased the relative risk of death 17-fold compared to those with well-preserved kidney function [2]. A more recent US study found a graded association, with the fastest rates of RKF loss being associated with doubling of all-cause mortality [3]. Other reported benefits of RKF include improved wellbeing, better quality of life [4] and less need to remove high fluid volumes during dialysis sessions with reduced risks of intra-dialytic hypotension [5], cardiac stunning [6] and associated mortality risk [7, 8]. This link between RKF, volume management and outcomes is further supported by observational studies indicating that increased risks associated with failing to achieve target weight are bidirectional, implying that both over- and under-hydration are a threat to patients [9].

Given the value of RKF, it is surprising how few clinical trials have focussed on interventions to maintain it as a key benefit to HD patients – the exception being ultrapure water [10], which is now standard care. Worse than this, a frequently applied fluid management strategy is to reduce the post-dialysis target weight until minimal or no anti-hypertensive drugs are required as evidence of adequate control of volume status. Our recent survey of fluid management practice patterns in UK units indicates that this is still being pursued in the majority of units [11], despite the risk it poses to residual kidney function by setting in place a continuing vicious cycle of volume depletion, excessive thirst and high inter-dialytic fluid gains.

The introduction of bioimpedance (BI) technology, such as BI spectroscopy, provides clinicians with the opportunity to break this cycle while avoiding the risk of excessive overhydration. BI gives additional information about body composition available at the bedside [12]. The principle is simple and involves the passing of a low-strength alternating current through the subject’s body to measure the resistance and reactance to flow. These two measures are dependent on the amount of fluid and cell membranes between the electrodes (usually placed on the hand and foot on one side of the body). The measurements are then modelled using information such as the subject’s weight and height to estimate the total volume of fluid in the body and the proportion of this that is within cells or in the extracellular space. In dialysis patients, compared to healthy subjects, the total amount of fluid (intra plus extracellular) can be high or low, but often the latter because of muscle wasting, inflammation or even over-aggressive fluid removal on dialysis. However, if the extracellular fluid is disproportionately high, this is a strong signal for an increased mortality risk [13–15]. For this reason, until now trials conducted to establish the clinical value of BI in setting target weights have focussed on clinical endpoints associated with hypervolaemia, such as high blood pressure, left ventricular mass and pulse- wave pressure or worsening extracellular to intracellular fluid distribution. The results of these interventions have been mixed, and more trials are clearly needed, but the price for achieving lower blood pressure through post-dialytic hypovolaemia was accelerated loss of RKF in one such study [16]. There is also evidence that presence of RKF leads to more stable fluid status without intervention in peritoneal dialysis patients [17]. Thus, BISTRO will establish the potential for BI to add value to fluid management and address the concern that this technology may be being adopted indiscriminately without clear evidence of benefit and a potential risk of harm.

## Methods/Design

### Aim

To determine if incorporation of bioimpedance spectroscopy-derived information on body composition into the setting of the post-dialytic target weight reduces loss of residual kidney function in incident centre-based HD patients, with the potential to improve clinical outcomes, dialysis-related symptoms, hospitalization and survival.

### Trial design

A pragmatic, multicentre, open-label prospective randomized controlled trial comparing current best practice in setting the post-dialytic target weight (control group) with the same assessment guided by serial BI measurements (intervention group). BI readings will be taken in both study groups but the results concealed from the clinical teams and trial participants in the control limb. To minimize performance and information bias, the BI measurements will be taken independently from the fluid assessments by trained nurses but within the previous week (i.e. the last 3 dialysis sessions), usually before sessions.

### Study setting

The study will take place in adult, out-patient haemodialysis centres, both main and satellite units, and their associated inpatient renal units during hospital admissions. Patients admitted for inter-current problems while participating in the trial will remain in the study and be assessed according to randomization. Participating sites will be available on the dedicated trial website, www.keele.ac.uk/bistro.

### Eligibility criteria

**Inclusion criteria**
Adults aged >18 years within 3 months of commencing centre-based maintenance haemodialysis due to advanced kidney disease CKD stage 5, planned or unplanned, via arteriovenous fistula, graft or central venous catheter (i.e. with or without permanent vascular access)Commencing dialysis on any regimen, including having incremental dialysis initiationResidual kidney function: Patients who have not yet started, but are about to start, dialysis treatment should have a daily urine volume > 500 ml/day *or* a measured mean urea and creatinine clearance ≥3 ml/min/1.72 m^2^ determined from a 24-h collection. Patients already on dialysis should have a urine volume >500 ml during the short inter-dialytic period *or* a measured mean urea and creatinine clearance ≥3 ml/min/1.72 m^2^, determined from the same timed inter-dialytic urine collections and an average of the post and pre dialysis plasma urea and creatinine concentrations.

**Exclusion criteria**
Unable or unwilling to give informed consentUnable to comply with trial procedures, e.g. collection of urine outputLikely survival prognosis or planned modality transfer < 6 monthsSubjects with limb amputations when the foot is not accessible *and* it is not possible to take hand to hand measurements

### Intervention

The study intervention is the incorporation of bioimpedance technology-derived information about body composition into the clinical assessment of fluid status of dialysis patients. The study intervention is the use of this additional information, specifically the *normally hydrated weight*, in conjunction with usual clinical judgement to set a target dry weight that is as close to normal at the end of a dialysis session, thus avoiding the risks of over- or under-hydration.

BISTRO is investigator-led with no input into the study design from industry. Based upon clearly defined criteria articulated in the original grant application, 6 device manufacturers were invited to submit proposals to a panel comprising experts, patient and lay representation and independent clinician and National Health Service experts. The Fresenius Body Composition Monitor (Fresenius BCM) was the device selected based on best validated device in the renal population both against gold standard methods (*i.e.* DEXA scanning, deuterium and sodium bromide solution) [18] and in referencing body composition of the dialysis patients to population norms [15, 19]. The BCM was originally CE-marked to Fresenius Medical Care as a Class IIa medical device in 2003; the CE mark was last updated in June 2011 [20].

All participating centres will receive bespoke training at the site visits prior to enrolling patients, which will include interpretation of BI data for use by fluid management assessors and a standardized approach to taking BI measurements by the research nurses. The study team will provide support for data interpretation throughout the study (see responsibilities).

### Outcomes

**Primary Outcome: Preservation of Residual Kidney Function**
Time to anuria, defined as urine volume ≤100 ml/day or ≤200 ml in the short inter-dialytic period confirmed by a further collection after 2 weeks to exclude temporary illness.

**Secondary Outcomes**
The rate of decline in kidney function, defined as the slope in decline of the average residual urea and creatinine clearance.Significant events, including vascular access failure and associated interventions, cardiovascular events, hospital admissions and death, including long-term legacy effects beyond trial completion using data linkage.Objective measures of dialysis efficacy and safety: e.g. inter-dialytic fluid gains, intra-dialytic hypotension, urea-reduction ratios (routine data)Patient-reported outcomes, including quality of life: EQ-5D-5 L; [21] SF12 [22], dialysis-related symptoms (Integrated Palliative Care Outcome Scale- Renal, IPOS) www.pos-pal.org, Patient Activation Measure [23], Duke Activity Status index [24], Montreal Cognitive Assessment (MoCA) [25], Client Service Receipt Inventory (CSRI) for Chronic Disease.Cost-effectiveness of the intervention, expressed as incremental cost per additional quality-adjusted life year (QALY) gained.

### Participant timeline

Trial entry for all participants is at the point of commencing centre-based haemodialysis as an outpatient, see Fig. 1. At this point trial eligibility will be confirmed, followed by randomization. All participants will be followed up until study completion or withdrawal because of death, transplantation, stopping dialysis (e.g. recovery of function) or patient choice, including any period after they reach the primary outcome so that the health economic analysis can be completed. The schedule of trial assessments is shown in Table 1.

**Fig. 1 Fig1:**
[figure not shown]
Schema for BISTRO Trial

**Table 1 Tab1:** Schedule of visits and procedures

	VISITS (Months) All undertaken at routine dialysis sessions						Urine Collections	Trial completion	Event based
Procedure	Visit −1	BaselineVisit 0	Visit 1	Visit 2	Visit 3	Visits 4–11 At 6,9,12,15,18,21,24 Months.	At 5,7,9,11,13,15,17,19,21,23,24 months. includes extra 2 weeks after primary endpoint is reached		
Eligibility	x								
Consent	x								
Residual kidney function tests for normalized GFR (urine volume and urine + blood to lab)	x		x	x	x		x		
Height (cm)	x								
Web-based randomisation		x							
Date of birth		x							
Ethnicity		x							
Sex		x							
Full medication list		x							
Primary Renal Disease Diagnosis		x							
Stoke comorbidity score		x							
Renal Registry comorbidity fields		x							
Planned/unplanned start		x							
Access type (fistula/graft/line)		x							
HD modality: (HD, HDF)		x							
Incremental/full start dialysis		x							
Transplant wait listed		x							
Dialysis prescription		x							
Bioimpedence with full dataset using software		x	x	x	x	x			x if indicated
BISTRO Study intervention record		x	x	x	x	x			x if indicated
Duke Activity Status Index (ASI)		x			x	x			
Patient Activation Measure (PAM)		x			x	x			
EQ-5D-5 L		x			x	x			
IPOS-Renal patient version		x			x	x			
Haemodialysis symptoms questionnaire		x			x	x			
Short Form (SF-12) Health Survey		x			x	x			
CSRI CKD		x			x	x			
Cognitive Assessment (MoCA)		x					x annually		
Study Termination/completion form								x	x
Adverse events									x

### Sample size

#### Primary outcome (time to anuria)

It can be determined from cohort studies and data collection from a large dialysis unit of 615 patients that the proportion of incident centre-based HD patients anuric by 10 months is in the region of 30% (range 25–67%) [26–30]. Sample size is based on a cumulative 10-month incidence of anuria of 30% in the control group and 20% in the treatment group and 11% competing risks (based on death and transplantation data extrapolated from the 2013 UKRR report [31]). Assuming exponential decline, proportional hazards, 90% power and 5% two-tailed significance, 185 events are required to detect the corresponding hazard ratio, with 12 months accrual and 12 months follow-up. This will require a total of 516 patients to be randomized 1:1, allowing for a 5% loss to follow-up.

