#### Primary outcome

Time to anuria will be analysed on an intention-to-treat basis (as the primary analysis) and on an as-treated basis (as the secondary analysis) using competing risks survival analysis [32], to estimate the relative risk (as expressed by the sub-hazard ratio) of the outcome (anuria) in patients where BI is used compared to control patients, accounting for the competing risks (death, transplantation). Patients undergoing modality change or recovery will be censored at the point of treatment switch. The analysis will control for known baseline covariates affecting residual function [26, 29], i.e. age, race, sex, comorbidities (separately or using a validated scoring system), antihypertensive drug use (ACE inhibitors/ARBs, calcium antagonists) and diuretic use.

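### The 185 events give 90% power for a cause-specific hazard ratio of 0.620, but the primary analysis estimates a sub-hazard ratio, for which power is about 87–89%; that ratio is also mislabelled a relative risk (minor)

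*Protocol article*

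**What the plan says.** In the protocol article, Sample size, Primary outcome (time to anuria), the design rests on a "cumulative 10-month incidence of anuria of 30% in the control group and 20% in the treatment group and 11% competing risks". It continues "Assuming exponential decline, proportional hazards", with "90% power and 5% two-tailed significance", and concludes that "185 events are required to detect the corresponding hazard ratio", "with 12 months accrual and 12 months follow-up". This leads to "a total of 516 patients to be randomized 1:1", "allowing for a 5% loss to follow-up". The hazard ratio is not given as a number. Nor does the section say whether it is cause-specific or on the subdistribution scale.

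Under Statistical methods, Primary outcome, the primary analysis is a competing-risks model with death and transplantation as the competing events. Its purpose is "to estimate the relative risk (as expressed by the sub-hazard ratio) of the outcome (anuria"). The model is adjusted for baseline covariates.

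**The concern.** With competing events there are two hazard ratios for anuria. The cause-specific ratio compares rates among patients still alive, not transplanted and not anuric. The sub-hazard ratio keeps patients who died or were transplanted in the risk set, so it tracks the cumulative incidence. The two ratios differ on the same data, and so does the number of events needed for a given power. If the trial was sized on one and is analysed on the other, the stated power belongs to an analysis that is not the primary one.

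The label is a separate matter. A sub-hazard ratio is not a ratio of risks. When anuria is as common as assumed here, the sub-hazard ratio lies further from 1 than the risk ratio, so calling it a relative risk invites a reader to overstate the effect.

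**Working it through.** **Inputs** (Sample size section): anuria at 10 months 30% control and 20% intervention; competing events 11%; two-sided 5%; 90% power; 12 months' accrual plus 12 months' follow-up; 5% loss; 1:1 allocation. Assumptions added here because the text does not settle them: the 11% applies in each arm, accrual is uniform, and cause-specific hazards are constant.

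**Step 1: the hazards.** With anuria incidence p and competing incidence q at 10 months, the total hazard is −ln(1 − p − q)/10, split in the ratio p:q.
- Control: −ln(0.59)/10 = 0.05276; anuria hazard 0.05276 × 0.30/0.41 = 0.0386 per month.
- Intervention: −ln(0.69)/10 = 0.03711; anuria hazard 0.03711 × 0.20/0.31 = 0.0239 per month.
- Cause-specific hazard ratio: 0.02394/0.03861 = 0.620.

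**Step 2: reproduce the events.** Schoenfeld's formula is 4(1.960 + 1.2816)²/(ln HR)² = 42.03/(ln HR)². At HR 0.620 (0.6201 before rounding), ln HR = −0.4779, which gives 184.02 and rounds up to **185**.

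**Step 3: reproduce the patients.** Averaged over follow-up times uniform on 12 to 24 months, the probability of observed anuria is 0.4439 (control) and 0.3116 (intervention), mean 0.3777. Then 185/0.3777 = 489.7, and 489.7/0.95 = 515.5, so **516**. Both published figures are recovered.

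**Step 4: the same inputs on the scale analysed.** The sub-hazard ratio implied by the cumulative incidences is ln(1 − F₁)/ln(1 − F₀), where F₁ is the intervention incidence and F₀ the control incidence.

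| Months | Anuria, control | Anuria, intervention | Sub-hazard ratio | Risk ratio |
|---|---|---|---|---|
| 10 | 30.0% | 20.0% | 0.626 | 0.667 |
| 18 | 44.9% | 31.4% | 0.634 | 0.701 |
| 24 | 52.5% | 38.0% | 0.642 | 0.724 |

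**Step 5: events and power on that scale.** Power with 185 events is Φ(√(185/4) × |ln HR| − 1.960).

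| Ratio | Events for 90% power | Power at 185 events |
|---|---|---|
| 0.620 (cause-specific) | 185 | 90.2% |
| 0.626 (sub-hazard, 10 months) | 192 | 89.1% |
| 0.630 | 197 | 88.1% |
| 0.634 (sub-hazard, 18 months) | 203 | 87.3% |

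No sub-hazard variant tried gave 185 events.

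**Step 6: simulation.** In 15,000 trials of 490 patients under the Step 1 hazards, with competing events kept in the risk set until administrative censoring, the average sub-hazard ratio was 0.631 and power was 87.3% (Monte Carlo standard error 0.3 points). The cause-specific test on the same data had 90.2% power. If the competing hazard is equal in both arms, instead of the 11% incidence, simulated sub-hazard power is about 88–89%. If all 516 patients are followed without loss (about 195 events), it is 88.8% under the Step 1 hazards.

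**The case against.** The strongest reply is that the gap is small and depends on assumptions. The article does not say on which scale hazards are proportional or how the 11% applies by arm. If proportionality is placed on the sub-hazard scale at the 10-month value, power is 89.1%. Small changes in the inputs matter more. An intervention incidence of 20.5% instead of 20.0% moves the cause-specific ratio to 0.638 and power at 185 events to 86.4%. The article itself gives a range of 25–67% for the proportion anuric by 10 months. Covariate adjustment was not modelled here and could move power. All of this stands, and it is why the result is a range and the point is minor. It does not make 185 events the right number for a sub-hazard ratio.

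On the label, the parenthesis in the methods text does name the sub-hazard ratio, so the estimand is identified. That stands too; the fault is one of description.

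Three stronger readings are tempting, and the documents do not support them.
- **The trial is underpowered and needs more patients.** A shortfall of 1 to 3 points does not carry that.
- **The trial will report a 36% reduction where the true one is 28%.** The 24-month figures (0.642 and 0.724) show how far the two measures differ, but no result is reported and the text does not commit that misreading.
- **A harmful effect on death could pass as less anuria.** A sub-hazard ratio does fall when competing events rise, but nothing in the article suggests such an effect, and death is listed as a secondary outcome and analysed separately among the critical events.

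The absence of cause-specific ratios and cumulative incidences is not an error either. Such reporting can be left to the statistical analysis plan, which the article refers to and which is not shown.

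**Conclusion.** The point holds as a minor one. The published 185 events and 516 patients follow from a cause-specific hazard ratio of 0.620. A few neighbouring cause-specific variants (0.623–0.624, 189 events) come close. For the sub-hazard analysis that the protocol makes primary, 185 events give about 87–89% power. The lower end holds under constant cause-specific hazards with 11% competing incidence in each arm, which is the model that reproduces the published figures. The upper end holds if the 10-month sub-hazard ratio of 0.626 applies throughout. Neither end allows for covariate adjustment. Separately, describing the sub-hazard ratio as a relative risk is wrong on the design's own values: 0.626 against 0.667 at 10 months. The label has no bearing on the sample size.

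**What to change.** - **Sample size, Primary outcome:** state the hazard ratio used (0.620) and that it is cause-specific. Add that power for the planned sub-hazard analysis with 185 events is about 87–89%, with the assumptions behind that range.
- **Statistical methods, Primary outcome:** delete the relative risk wording and call the estimate a sub-hazard ratio.
- **Optional, for the statistical analysis plan:** show cumulative incidences and cause-specific hazard ratios beside the sub-hazard ratio.

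The cost is two edited sentences and a stated power 1 to 3 points lower. No patients are added and the primary analysis does not change.

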#### Secondary outcome

The rate of decline in renal clearance is reported by most studies as a monthly decline of 0.3 ml/min/1.73 m^2^/month (reported range 0.3–0.4) [26–30]. At the same significance level, this sample size would provide just under 95% power to detect a difference in rate of 0.05 ml/min/1.73 m^2^/month, assuming linear change assessments at 0,1,2,3,5,7,9,11 and 13 months, and a (conservative) autocorrelation of 0.30.

